##### Office-GAP intervention (patient activation intervention)

We have described the Office-GAP intervention in previous peer-reviewed publications [9, 10, 21]. Briefly, after recruitment, patients in the Office-GAP group will attend (1) one scheduled group visit (90–120 min; 4–6 patients at a time), conducted by the research assistants and (2) follow-up visits with their primary care providers within 1 month and then at 3, 6, 9, and 12 months after the group visit. At these follow-up visits, providers will complete the Office-GAP Checklist, which evaluates medication prescribing behavior. In addition, SDM and goal setting occurs between patient and provider. These follow-up visits are patients’ regularly scheduled visits with their primary care providers (PCPs) and not additional to their usual care.

##### At the group visit

We will obtain informed consent/HIPAA authorization from patients after introducing them to the study: Group 1: Office-GAP + Texting session: the group visit is a shared decision-making (SDM) activation session wherein patients learn self-management behaviors, communication skills, and use of decision support tools (DSTs). They also learn how to use the eCap electronic pill container to monitor medication adherence: learn to use Way2Health Texting service and confirm set up on their mobile phone. Group 2: For the texting only group: participants will learn how to use Way2Health Texting service and confirm set up on their mobile phone and learn how to use the eCap electronic pill container to monitor medication adherence. They will not experience the Office-GAP intervention. Both groups will also complete baseline study questionnaires during the group visit.

##### Office-GAP follow-up visit with providers

The Office-GAP Checklist is the core tool of our SDM intervention. A one-page checklist, this SDM tool outlines all evidence-based medications for secondary prevention of CVD in T2DM patients. It is an in-consultation decision support tool that helps engage the patient and provider to encourage and enhance an SDM process via discussion of medication and secondary prevention/lifestyle changes during an office visit. In this study, the Office-GAP Checklist will be completed by the physician with direct patient involvement during the office visits at 0–1, 3, 6, 9, and 12 months. Only group 1 patients will use this checklist during their office visits.

The Office-GAP Checklist also serves as a physician reminder at the point of care, because the physician records a checkmark for each medication: “Yes” (if patient is on the medication), “No” (if patient is not), or “Does not apply to me because….” A reason for exclusion of a medication is also provided (patient is not eligible for the medication, has a contraindication to its use, or the patient and physician have identified an alternative due to side effect or cost concerns). Details about the next appointment and any secondary prevention plan changes are also listed on the form. At the end of the visit, both patient and physician sign the form to confirm that they have reviewed the checklist. The patient receives a copy of the checklist to take home and a copy is retained in the patient record. All providers in the intervention teams receive a brief physician education in Office-GAP tool use and communication skills.

Educational tool literacy standards: Office-GAP has been rigorously adapted for use with low health literacy patients. All study materials are grade 6 reading level.

##### Mobile DM self-management texting intervention (Way2Health)

During group visits, all patients in both groups will be taught how to send and receive text messages on their phone. The Way2Health service does not require patients to use a special app. Way2Health engages patients in two ways: (1) Patients receive daily Way2Health messages appropriate to their diagnosis and medications (e.g., BP, blood glucose, medication) and appointment reminders throughout the study. They also receive informational and educational texts. (2) Patients respond to prompts that RAs monitors. In addition, they receive messages to contact their provider’s office with questions or concerns throughout the study via texting. Patients will receive additional diabetic modules that follow the standard for diabetes education for the rest of the 12 months once the initial 15-week program is complete. We will use the Way2Health texting program to encourage T2DM patients to maintain communication with their providers, improve medication adherence, and other secondary prevention and self-care between visits. Daily messages may take the form of reminders, prompts, education, or reinforcement. Sample message texts include “Did you take your medications today?” and “How many times did you check your feet for wounds this week?” Our pilot found the program to be usable and effective.

##### Provider and practice staff training

All intervention providers will participate in an interactive orientation which we have shown to promote behavioral change among health professionals. Providers will be asked to give their consent to participate in the study during this session. Provider/Staff Educational module: The training session is 60–90 min [22]. The session is scheduled multiple times to meet providers’ needs. In our pilot Office-GAP study, we achieved 100% participation by providers. The training module, facilitated by PI and co-investigators, includes (1) brief presentations on effectiveness and cost-effectiveness of medical therapy and behavior changes in management of T2DM, blood pressure, and heart disease; (2) a hands-on practice session for providers to elicit patients’ preferences and values; (3) an introduction to the Office-Gap Checklist and best practices for using it during a patient encounter; and (4) review of the Smith evidence-based patient-centered method for establishing trust, communicating clearly, and engaging in goal-setting with patients [22]. Providers will have a chance to practice skills using Braddock [23] and Elwyn’s [24]) approach to role-playing to model office visits; and (5) a complete pre-and post-training survey (before and after the training session) to determine provider attitudes about the use of DSTs, SDM, and mHealth in their practice and an end of study semi-structured interview.

#### Criteria for discontinuing or modifying allocated interventions {11b}

We try to keep modifications and discontinuation to a minimum in this pragmatic trial. However, if a patient does not consent or withdraws consent from a component of the study, or if a caregiver takes over administration of medications, these may be conditions for disenrollment. Our pragmatic trial takes every opportunity to document any barriers to implementation such as interruptions in cell phone service, scheduled hospitalizations, family vacations, etc., without disenrolling.

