### Implementation {16c}

The statistician generated the allocation sequence, and all clinical staff were notified prior to enrolling patients. Because this is a cluster randomized trial, all patients at a particular team will be in the same arm. Patients are enrolled by the RA assigned to each clinic after signing the informed consent agreement.

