## Assignment of interventions: blinding

### Who will be blinded? {17a}

After the 17 teams are randomly assigned to the two arms, neither trial participants nor the care providers can be blinded to the assignment due to the nature of the intervention. Neither the participants nor the researchers are blinded for this study.

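### Section {11b} lets unblinded staff disenrol patients who withdraw from one component or whose caregiver takes over medication, so outcome loss after randomisation could differ by arm

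*Protocol article*

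**What the plan says.** The protocol article, section {11b}, opens by saying that discontinuations will be kept to a minimum. It then names two triggers, "if a patient does not consent or withdraws consent from a component of the study, or if a caregiver takes over administration of medications", and adds that "these may be conditions for disenrollment". Other disruptions are treated differently: the trial will document "interruptions in cell phone service, scheduled hospitalizations, family vacations, etc., without disenrolling".

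Four other places bear on how this rule works.

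- **Timing.** Implementation {16c}: "The statistician generated the allocation sequence, and all clinical staff were notified prior to enrolling patients".
- **Blinding.** Section {17a}: "Neither the participants nor the researchers are blinded for this study".
- **Components by arm.** Both arms attend a group visit and receive texting, eCap, surveys and blood pressure checks. Group 1 adds the activation session and the Office-GAP checklist: "Only group 1 patients will use this checklist during their office visits". Of the texting-only group, the group visit section says: "They will not experience the Office-GAP intervention".
- **Analysis.** The design section targets 320 evaluable patients. Section {20c} covers missing responses through likelihood methods under missing at random and through inverse-probability weighting, and does not mention disenrolment. The article nowhere says that disenrolled patients stay in outcome collection.

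**The concern.** A patient who stops one part of an intervention, or whose pills are now handled by someone else, is still a patient of a randomised team. Ending that patient's participation, rather than only the part that has stopped, makes a change in intervention status into a loss of outcome data.

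Three features make this more than ordinary attrition. First, the triggers sit close to the primary outcome: refusing a component is a form of disengagement, and caregiver take-over changes how medication is taken and what eCap records. Second, disenrolment is optional, no criterion is given for when it applies, and nobody involved is blinded. Third, the arms do not have the same number of components, so the first trigger has more ways to occur in group 1.

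At stake is selection after randomisation in the adherence comparison. A later analysis plan could promise analysis as allocated, but it could not recover outcomes that were never collected.

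**Working it through.** **1. The stated figure that disenrolment touches.** The sample size section inflates 320 patients for attrition of 10%, 4% and 2%:

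320 / (0.90 × 0.96 × 0.98) = 320 / 0.84672 = 377.9, so 378.

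The recruitment target reproduces. The allowance has no spare margin, but the article does not say whether disenrolment is counted inside it.

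**2. The planned contrast.** Projected adherence at 12 months is 0.65 in group 1 and 0.42 in group 2, a difference of 0.23. At 6 months it is 0.62 − 0.42 = 0.20.

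**3. Illustrative bias.** The documents give no disenrolment rate and no adherence level for those removed, so both are assumed. Let d₁ and d₂ be the shares removed in groups 1 and 2, and g the amount by which removed patients fall below those who stay. If removed patients contribute no outcome, each arm's mean rises by d × g, and the contrast shifts by (d₁ − d₂) × g. With g = 0.30:

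| Removed, group 1 vs group 2 | Shift | Share of 0.23 |
|---|---|---|
| 5% vs 2% | 0.03 × 0.30 = 0.009 | 4% |
| 10% vs 3% | 0.07 × 0.30 = 0.021 | 9% |
| 5% vs 5% | 0 | 0% |
| 2% vs 5% | −0.03 × 0.30 = −0.009 | −4% |

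The last row shows that the sign follows whichever arm loses more.

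**4. A second parameterisation.** Suppose there is no true effect, both arms have mean adherence μ = 0.42, and removed patients average a = 0.10 to 0.30. The observed arm mean is (μ − d·a)/(1 − d). For example, with a = 0.10 and removal of 10% vs 5%:

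(0.42 − 0.010)/0.90 − (0.42 − 0.005)/0.95 = 0.4556 − 0.4368 = 0.019.

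Over the range of a, the spurious difference is:

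- 5% vs 5%: 0.000
- 10% vs 5%: 0.007 to 0.019
- 15% vs 10%: 0.008 to 0.021
- 15% vs 5%: 0.015 to 0.040

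**5. Conditions for no bias.** Equal rates are not enough if different kinds of patient are removed. With 5% removed in each arm, but g = 0.30 in group 1 and 0.10 in group 2, the shift is 0.05 × (0.30 − 0.10) = 0.010. If caregiver take-over raises recorded adherence, g is negative for that trigger and its contribution changes sign.

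**The case against.** The strongest reply is that the rule is milder than it looks. It is permissive, follows a commitment to keep discontinuations few, and retains patients through many kinds of disruption. This stands: a reader might infer that the rule removes every such patient and turns the trial into a per-protocol comparison, but the text does not say so.

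Second, not consenting at the group visit is partly non-enrolment, because patients are enrolled only after signing consent. This also stands, and it limits the point mainly to later withdrawal from a component and to caregiver take-over.

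Third, a reader might infer that group 1 will lose more patients and that the bias favours it. The documents do not support that. The extra components create an opportunity, not a documented difference. The retention plan pays $100 in group 1 and $50 in group 2 at the 12-month visit, which may work the other way. Nothing suggests that take-over is more common in either arm.

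Fourth, caregiver take-over has a measurement rationale: eCap openings may then reflect the caregiver, while the outcome is defined by the patient's own medication taking. That is a reason to flag and examine those data. It is not a reason to stop collecting chart, survey and clinical outcomes.

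Fifth, no section says that data collected before disenrolment are discarded, and the mixed model and weighting could use them. This is correct but limited. Post-baseline eCap adherence is built at 6 and 12 months and baseline uses a proxy, so a patient removed before month 6 may contribute no post-baseline primary value. Missing at random is doubtful if removal depends on current, unrecorded adherence.

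Finally, a reader might infer that these losses come on top of the planned attrition. The sample size section does not say so; they may be included in it.

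**Conclusion.** The point holds as a risk created by a stated rule. Section {11b} permits unblinded, discretionary disenrolment after team randomisation, on triggers plausibly related to adherence, with more components to withdraw from in group 1. The article says nothing that keeps such patients in follow-up.

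The direction and size of any bias are unknown. The 0.01 to 0.02 illustration (4 to 9% of the planned 0.23) rests wholly on assumed removal rates, an assumed 0.30 adherence gap, no outcome data from removed patients, and no correction by the model or weighting. The wider scenarios in the working reach 0.040. Bias is nil if removal is equal and the removed patients are similar. This is a modest threat that is cheap to close. It does not invalidate the design.

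**What to change.** Amend {11b} to separate stopping a component from leaving the trial:

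- Withdrawal from a component ends that component only.
- eCap, chart and 6- and 12-month outcome collection continue unless the patient withdraws consent for data collection.
- All enrolled patients are analysed in the arm of their team.
- Caregiver take-over is recorded with its date and the patient stays in follow-up. A sensitivity analysis examines how post-take-over eCap data affect the adherence contrast.

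The cost is protocol and analysis wording, plus one dated field in the data forms. The downside is that some eCap data will reflect caregiver dosing, which the flag and the sensitivity analysis make visible. The trial status section expects recruitment to finish around April 2024, so the earlier the change, the more outcome data it saves.

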#### Strategies to improve adherence to interventions {11c}

##### Intervention integrity

Following the framework of Borrelli et al. [25], treatment fidelity ensuring the reliability and validity of Office-GAP and Texting will be maintained by (1) Decision Support Tool (DST) design; (2) training providers; (3) training and monitoring RAs; (4) delivery of educational modules during the group visits and use of mobile phones and DSTs; (5) receipt of DSTs and educational modules; use of study operating procedure manuals; and (6) intervention skills will be monitored by the PI/Project Manager. Intervention content quality will be monitored at weekly research team meetings. These measures will help ensure successful transferability to other settings [26].

Mobile service engagement is monitored on the W2H dashboard by RAs who can see responses from participants; data management oversight in RedCap to ensure that scheduling of patient visit milestones are being met.

#### Relevant concomitant care permitted or prohibited during the trial {11d}

Patients must not be enrolled in another cell phone intervention or behavioral diabetes management program.

Other relevant concomitant care for cardiovascular disease or diabetes is not excluded.

#### Provisions for post-trial care {30}

Because of increased monitoring from the Office-GAP program and short text messages, we might detect more episodes of elevated glucose or BP. Patients will be told by the RA under supervision of the PI, an Internal Medicine physician, to contact their PCP for immediate intervention and management of any abnormal blood glucose or BP.

We do not anticipate any substantial psychological risks to be associated with participation in this study. There are no financial or legal risks associated with this study.

### Outcomes {12}

All data will be collected at baseline, 6 months, and 12 months (Table 2). Our primary outcome is medication adherence measured using eCAP electronic monitoring and self-report. Secondary outcomes are (a) diabetes-specific 5-year CVD risk as measured with UK Prospective Diabetes Study (UKPDS) Engine score; (b) provider engagement as measured by CollaboRATE Shared-Decision Making measure; and (c) patient activation measures (PAM).

**Table 2 Tab2:** Measures table

Variables	Instruments	Methods	Analysis	Time
**Knowledge and attitude about patient-centered care, SDM, use of DSTs**	**Pre and post survey of providers** **Semi-structured interviews**	**90 min. CME interactive orientation sections with providers and exit interviews**	**Descriptive pre-post analysis** **Thematic analysis of transcribed interviews using Dedoose**	**Pre and post physician education** **End of study**
**Medication adherence**	**Medication Events Monitoring Systems ( eCap).** **Cronbach’s alpha=.0.85** **ARMS Survey**	**eCap upload to BRIC** **RA will administer form to patient pre/post intervention to evaluate treatment medication adherence**	**Linear or generalized linear mixed effects model and Beta regression to evaluate changes over time for groups 1 and 2**	**Baseline, 6 and 12 months**
**Patient Activation Measure Scores/Level**	**Patient Activation Measure (PAM) Cronbach’s alpha=.91**	**RA administers form to patient pre and post intervention**	**Linear or generalized linear mixed effects model for change overtime for groups 1 and 2**	**Baseline, 6 and 12 months**
**Self-Efficacy Scores**	**Stanford 6-Item Self Efficacy Scale** **Summary DM Self-Activities Measure (SDSCA)**	**RA administers form to patient pre and post intervention to evaluate change in self-efficacy**	**Linear or generalized linear mixed effects models for change over time for groups 1 and 2**	**Baseline, 6 and 12 months**
**Rate of use of aspirin/antiplatelets, beta-blockers, ACEI/ARBs, cholesterol assessment and treatment, DM medications**	**PAI agreement in chart** **Patient medication list** **Patient medical record** **Texting log**	**Chart audits to compare the rate of use of aspirin/antiplatelets, beta-blockers, ACEI, cholesterol assessment and treatment of DM**	**Linear or generalized linear mixed effects model for change overtime for groups 1 and 2**	**Baseline, 6 and 12 months**
**Rate of BP control** **Diabetic Control (HbA1c)**	**Digital sphygmomanometer , HbA1c assessment in the community lab using standard instrument**	**Three BP measurements, 1 minute intervals, using appropriate cuff Reliable point-of-care HbA1c test**	**Linear or generalized linear mixed effects model for change overtime for groups 1 and 2**	**Average BP and HbA1c at baseline, 6 and 12 months**
**Combined Outcome Measure for Risk Communication & Treatment Decision Making Effectiveness (COMRADE)**	**COMRADE questionnaire** **Cronbach’s alpha=.92** **CollaboRate SDM Measure**	**RA administers form pre/post intervention to evaluate satisfaction with shared decision-making**	**Linear or generalized linear mixed effects model for change overtime for groups 1 and 2**	**COMRADE use at baseline, 6 and 12 months**
**PAI + Texting use rate & acceptability rating by clinical staff**	**PAI agreement forms; Texting log; pre/post physician/staff surveys; physician/staff interviews**	**RA records and chart abstraction to determine PAI + Texting use** **Staff meeting and survey to explore adoption + practice diary entries**	**Determine rate of use of PAI +Texting** **Frequencies of responses to evaluation surveys**	**Chart Abstraction at 6 months. RA tracks rates throughout study**

#### Primary outcome

Medication adherence is defined by the adherence metric (ratio of the number of days in which a patient takes his/her medication as prescribed, to total number of days he/she is expected to take them in that period) [27, 28]. Since there is no ideal medication adherence measure, a multi-measure approach is often recommended in assessing medication adherence to maximize ecological validity [28]. A meta-analysis also showed that this approach, including using a self-report method, can increase sensitivity to non-adherence [28, 29]. The concomitant use of both objective and subjective measures will provide higher reliability and represents the most rigorous approach to assessing medication adherence [30]. We will measure medication adherence using the eCap electronic pill container: the most objective and valid method of assessing adherence [28, 31], and a self-reported adherence measures described below. eCap will record the number of times the pill bottle is opened daily, over the course of the study. As in other trials, patients will be given eCap to assess adherence to their most frequently taken CVD prevention medication (e.g., BP, blood sugar lowering or cholesterol-lowering medication) [32], as identified by the primary care physician (PCP). Studies have shown that adherence to one medication parallels adherence to others [33]. Any medications taken during emergency room visits or hospitalizations will be obtained from patient reports and chart abstraction of patient medical records to avoid erroneously penalizing patients when the eCap is not used. Such days will be removed from the denominator of the formula to compute adherence rates. Self-reported adherence will be assessed using Adherence to Refills and Medications Scale (ARMS) a 14-item scale with two subscales for taking medications as prescribed and refilling medications on schedule [34, 35].

#### Secondary outcomes

Secondary outcomes are as follows: (a) diabetes-specific 5-year CVD risk as measured with UK Prospective Diabetes Study (UKPDS) Engine score; (b) provider engagement as measured by CollaboRATE Shared-Decision Making measure; and (c) patient activation measures (PAM). The UKPDS score includes components we hypothesize will be improved by the intervention, including HbA1c, systolic blood pressure, cholesterol levels, and smoking status. Using a cardiac risk score allows us to quantify the cumulative impact of changes in multiple risk factors and translate changes in physiologic parameters to risk estimates that are meaningful to patients and policy makers [36]. Cardiac risk scores including the UKPDS Risk Engine have been successfully used as outcomes in multiple clinical trials [37–41] and validated in multiple populations [42]. A 1–2% overall change in risk can be considered clinically significant at a population level [43]. We will measure HbA1c using a portable Afinion AS 100 finger stick sample analyzer, which is accurate and has a coefficient of variation <5% as required by the National Diabetes Data Group [44].

